## Abstract

**Background:**

Adherence to allergen immunotherapy is important for its effectiveness. There is currently limited data available on allergen immunotherapy adherence outside of clinical trials i.e. in real-life clinical practice. As part of a European Academy of Allergy and Clinical Immunology Immunotherapy Interest group initiative, we endeavoured to design a survey in order to prospectively evaluate adherence to subcutaneous and sublingual immunotherapy across different European countries.

**Method/Design:**

The inclusion criteria for this prospective, multi-country survey were set as: adults, starting clinically indicated allergen immunotherapy for respiratory allergic disorders or Hymenoptera venom allergy. An online survey was designed in order to enrol participants and assess adherence to immunotherapy.

Eight countries (Czech Republic, Georgia, Germany, Greece, Italy, Poland, Portugal, Spain) were selected to reflect different parts of Europe and differences in allergens and routes of immunotherapy administration. Each country has an allocated National co-ordinator that has identified local Allergy departments willing to enrol participants in this survey.

Each participant will be followed up for a total of three years. In order to assess adherence, a 4-monthly follow-up form detailing any missed doses and reasons will be completed online. In case of a participant discontinuing treatment, reasons for this will be recorded.

**Discussion:**

The use of online survey software has enabled us to make this survey a reality and reach clinicians in different countries. Forty-five centres have enrolled a total of over 1,350 participants. It is hoped that this prospective real life survey will enable us to gain a better understanding of reasons that affect adherence to subcutaneous and sublingual immunotherapy and assist in developing ways to improve this.

## Introduction

The lack of adherence to medication is an emerging and worldwide problem in the treatment of chronic diseases. It is responsible for a decrease of treatment efficacy, increased hospitalisations, morbidity and mortality, and is a significant burden for patients as well as for society and healthcare systems [1]. Rates of treatment discontinuation are reported to be between 20-40% for acute illnesses, increasing to 30-60% for chronic conditions and reaching 80% in preventative interventions [2]. In the United States alone, costs due to lack of adherence have reached the figure of 100 billion dollars mainly due to unjustified hospitalisations [3]. Accordingly, medical research has been showing growing interest in this area. On PubMed, the number of studies concerning this subject has more than doubled within the last ten years, increasing from 1,349 in 2003 to 3,376 in 2013.

Adherence to treatment is the complex result of different determinants related to the patient, the disease, the therapy, the patient/physician relationship and the healthcare system [1,2,4]. All of these factors interact in different ways in a single individual. Furthermore, the complexity of the treatment schedule as well as the route of administration can negatively affect adherence [5,6].

Allergic rhinitis is a very common disease with a significant socio-economic burden, due to direct (medications and doctor visits) and indirect costs (loss of productivity/working days) [7]. Currently, the worldwide prevalence of allergic rhinitis in adults ranges from 10-30%, but in children it reaches 37% in Western countries [7]. Discontinuation of pharmacological therapy is a problem shared by allergic rhinitis as well as chronic illnesses [6]. As far as allergen immunotherapy (AIT) is concerned, adherence represents the most critical issue. AIT significantly reduces the clinical symptoms at an early stage as well as the use of concomitant medications, as reported by randomised controlled trials and meta-analyses [7,8]. However, only after a long-term course, whose recommended length is at least three years, it is possible to obtain a long lasting effect following withdrawal and to reduce the risk of development of asthma and/or new sensitisations [9-16]. Immunotherapy for Hymenoptera venom allergy usually lasts between three and five years. Adherence to this is thought to be higher given the life-threatening reactions to venom, however this has not been formally assessed [17].

Rates of adherence for individual patients are usually reported as the percentage of the prescribed doses of the medication actually taken by the patient over a specified period. However, the evaluation of adherence is far from standardised. In fact, many methods have been proposed to measure adherence. Each of them has advantages and disadvantages but none of these can be currently considered the gold standard [1]. Methods for assessing adherence to medication can generally be divided into three categories:Subjective measurements based on what is reported by the patient or caregiver. These methods, though inexpensive, are not completely reliable, as patients sometimes can deny the lack of regular medication intake.Objective assessment based on the count of pills or the examination of pharmacy refill records. The commonest drawback is that the absent pills are considered actually taken by the patients. The use of electronic devices can be more accurate, but too costly in daily life.Measurement of drug levels or drug metabolites in serum or urine. The feasibility of this method is limited to only a few drugs (such as digoxin, anti-epileptics, theophylline, lithium). For asthmatic patients on regular oral steroids the evaluation of serum cortisol can be helpful [6,18].

Besides these technical limitations, a further methodological disadvantage is that if the patients are aware that adherence is an outcome of the study a bias is immediately introduced [1]. For this reason adherence data from randomised controlled trials may not reflect a true representation as participants are strictly followed and observed. More consistent data are therefore likely to be collected from real life studies.

In addition, the wide heterogeneity of immunotherapy studies may account for the conflicting results and the difficulty in drawing definite conclusions. Studies published so far have been carried out in different populations, different countries and according to different designs (retrospective, cross sectional, prospective). Furthermore, patients were treated with various allergen extracts and according to different schedules. Moreover, the methods used to measure adherence were also dissimilar from study to study [19].

Interestingly, although an adherence rate is considered generally acceptable when higher than 80%, a general agreement on this cut off is still lacking [1,19].

Up to now, several studies have been published on subcutaneous immunotherapy (SCIT) [20-34] as well as on sublingual immunotherapy (SLIT) [35-46]. As shown in Tables 1 and 2, the adherence rate is generally low and it varies greatly for both SCIT and SLIT. Comparing the studies according to route of administration, a higher number of SLIT studies reported an adequate (>80%) adherence. On the other hand, SCIT studies included a larger population and were of considerably longer duration.

**Table 1 Tab1:** **Adherence studies for SCIT**

**Author**	**Study Population (pts)**	**Age (A/C)**	**Study duration**	**Adherence rate (%)**
Chon (1993) [20]	217	A	4 y	50
Lower (1993) [21]	315	C	4 y	56
Tinkelman (1993) [22]	3.349	C,A	1y	65
Ruiz (1997) [23]	247	A	18 m	62
Donahue (1999) [24]	603	C, A	4y	33
Rhodes (1999) [25]	1.033	A	3y	88
More & Hagan (2002) [26]	381	C,A	3y	77
Pajno (2005) [27]	1.886	C	3y	89
Hommers (2006) [28]	296	A	not stated	66
Hankin (2008) [29]	520	C	3y	47 (1 y) 16 (3rd y)
Mahesh (2010) [30]	100	A	not stated	58
Hsu & Reisacher (2012) [31]	139	A	4y	55
Guenechea (2013) [32]	156	A	5y	63
Kiel (2013) [33]	2.796	A	3y	23
Silva (2014) [34]	122	C, A	4y	54

A: adults, C: Children, Y: year, M: month.

**Table 2 Tab2:** **Adherence studies in SLIT**

**Author**	**Study population (pts)**	**Age (A/C)**	**Study duration**	**Adherence rate (%)**
Marogna (2004) [35]	319	A	3y	85
Lombardi (2004) [36]	86	A	18 m	79-97
Pajno (2005) [27]	806	C	3y	79
Passalacqua (2006) [37]	443	A	6 m	76
Passalacqua (2007) [38]	71	C	6 m	85
Cadario (2008) [39]	40	A	1y	65
Roder (2008) [40]	154	A	2y	77
Chang (2009) [41]	142	A/C	6 m	69
Jansen (2009) [42]	91	A	6 m	95
Ott (2009) [43]	183	A/C	2y	91
Vita (2010) [44]	300	C	2y	30-76
Pajno (2012) [45]	150	C	2y	54
Hsu & Reisacher (2012) [31]	139	A	4y	59
Kiel (2013) [33]	3.690	A	3y	7
Trebuchon (2014) [46]	736	C	2Y	86

A: adults, C: Children, Y: year, M: month.

Many reasons have been reported as being responsible for immunotherapy discontinuation. Among the patient related factors, a younger age and female gender appear to be more frequently related to non adherence [21,25,32,42] whereas severity of the disease seems not to affect the number of dropouts [27-41]. Among the causes for discontinuation, treatment costs are relevant for both subcutaneous and sublingual routes [21,23,26,31,34,37,38,40]. Local side effects following administration may account for SLIT discontinuation in children as well in adults [37,38,40,45], whereas inconvenience due to time consuming schedules, or fear of injections are mainly related to SCIT treatments [21,22,25]. In seasonal allergy, the use of cluster SCIT schedules [20,22] as well as a pre-co-seasonal treatment seem to favour a better adherence [39,40]. The overall analysis of these results does not appear to detect significant differences in adherence according to delivery route [19], but methodological and cultural heterogeneity of the studies currently do not allow for any firm conclusions.

Under the framework of the European Academy of Allergy and Clinical Immunology (EAACI) Immunotherapy Interest Group, we endeavoured to design a survey in order to prospectively evaluate adherence to subcutaneous and sublingual immunotherapy across different European countries. This will include AIT for respiratory allergic disorders as well as Hymenoptera venom allergy.

## Methods

### Objectives

The survey aims to assess adherence to AIT in a real life setting. The primary objectives are to prospectively evaluate the rate of adherence to AIT for inhalant allergies (sublingual and subcutaneous routes) and Hymenoptera venom allergy (subcutaneous) in a three year period in real life across different European countries. The secondary objectives are to identify reasons for lack of adherence and discontinuation of treatment and to explore possible reasons for differences in adherence rates in different countries and different individuals.

### Survey design

This is a prospective, multi-centre, observational survey. The survey will take place in eight countries: Czech Republic, Italy, Germany, Georgia, Greece, Poland, Portugal and Spain. These countries were identified as representative of different areas of Europe and also in order to include a variety of allergens contributing to allergic disease.

This is an online survey that will follow participants for a period of 3 years from the start date of AIT. It was decided to follow participants for a 3-year period as this is the usual length of AIT treatment and there is concern that adherence initially may be relatively good but this may decrease as time passes.

Initially approval for this project was sought from the EAACI Executive Committee. In order to initiate this survey, the two PASTE survey co-ordinators and the EAACI Immunotherapy Interest Group initially contacted the National Allergy Societies of the eight countries to inform them about this survey. Each National Allergy Society identified a "National survey Coordinator” that would be responsible for coordinating all local activities in that country. This involved duties such as identifying study centres willing to participate in the survey and dealing with national regulatory issues such as ethics and any other regulatory requirements.

In order for centres to be able to participate in the survey, they would need to have access to the internet and have an allocated physician in charge who will be in contact with the National survey Coordinator and who will be able to complete the survey questionnaire in English.

### Participant selection and procedure

The survey population consists of adults with IgE mediated respiratory allergies or Hymenoptera venom allergy who will be starting AIT (either SCIT or SLIT) according to accepted clinical standards of practice.

The inclusion criteria were set as: male or female, 18 years of age or over (no upper age limit) and being eligible for immunotherapy to inhalant allergens or Hymenoptera venoms. The exclusion criteria were previous AIT treatment at any time and any contraindications to receiving immunotherapy according to European standards of practice.

Each participating centre coordinator identified any potential participants and assessed whether they met these criteria. In order to enrol a participant, an online enrolment questionnaire was required to be completed by the physician. This form includes information about the participant, details about their allergies and treatment.

For each participant an online follow up adherence form will be completed by the local physician every 4 months. This adherence follow-up form includes questions regarding the number of missed doses, phase of the treatment at the time and any possible reasons for missed doses. The last adherence follow-up form will be completed at 36 months from AIT initiation.

In case of participant withdrawal, a discontinuation online form will be completed. This includes questions including the timing and any identified reasons for stopping AIT.

The enrolment period opened in December 2012 and closed in February 2014.

The study timeline is shown in Figure 1.

**Figure 1 Fig1:**
[figure not shown]
**Study timeline.**

### Questionnaire design

In order to identify the specific questions and areas to be investigated, the opinion and advice of experts in this field was sought at an EAACI PASTE meeting in Geneva 2012. At that stage, the content of the enrolment form, 4-monthly follow up form and discontinuation form was agreed.

The enrolment includes information about age, sex, education and employment status, allergen sensitisations, condition for which receiving immunotherapy, allergen, route and immunotherapy regime, date of AIT initiation, treatment setting, follow-up arrangements as well as funding for treatment.

For SCIT, recording of any missed doses is likely to be more accurate as participants have to attend the clinic to receive their injection and the physician is always aware of any missed doses or discontinuation. Follow up of SLIT patients varies in different countries and therefore a compromise was reached to enter follow-up data every 4 months as this would fit with the practice in some countries as well as not be a burden to the physicians who have to complete these forms in their own time without any specific funding. Depending on the practice of each country, other data such as pharmacy/prescription records, follow-up appointments and telephone contact will be used to improve patient reporting of any missed doses. It was felt that use of other methods such as treatment diaries may affect results by making patients more aware that they are participating in an adherence survey and thus affecting behaviours.

The follow up adherence form was designed to include questions regarding the number of missed doses in the previous four months, the phase of the treatment at the time i.e. up-dosing or maintenance and any possible reasons for missed doses. Reasons investigated included acute illness, forgetfulness, lack of efficacy, financial costs, time/work commitments, local reaction, systemic reaction, geographical constraints, new medical condition/s, pregnancy and other.

The discontinuation form also explored specific reasons for ending treatment.

The SurveyMonkey® online survey software was selected to be used for the enrolment and follow up data collection. This allows participating centres to enter data from different countries and enable collection in a central database. All data entered is protected by an enhanced security system (Secure Sockets Layer, SSL, a protocol for encrypting information over the Internet) [47].

The follow up survey forms used a skip logic pattern, allowing participating clinicians to avoid certain sections according to their responses in preceding questions.

The survey instruments were tested several times to ensure and improve their functionality and ease of use. Attention was also paid to user interface principles such as colours selected, number of questions per screen, formatting of text and logical structure of the questionnaire.

### Data management

All data collected by the participating centres is entered anonymously in a coded format in order to protect the participants’ identity. A specific country code was allocated to each country. An additional code beginning with the country code was allocated to each centre of that specific country. Furthermore, each participant was given a code incorporating both the country and centre code. This way the enrolment forms can be matched with all the 4-monthly follow up forms completed for each participant at the stage of data analysis.

The data is regularly assessed by the survey co-ordinators in order to check that it is being entered correctly.

### Data protection

In order to further protect the collected data, only the two survey co-ordinators have access to the password protected completed questionnaires. In case of any queries or mistakes made in the data entry, the survey co-ordinators can be contacted to check the entered data and make any necessary changes.

In addition, the SurveyMonkey® facility uses advanced technology for Internet security. To use this tool, as administrator, a unique user name and password must be entered. SurveyMonkey® issues a session “cookie” only to record encrypted authentication information for the duration of a specific session. Once the user accesses secured areas, the Secure Sockets Layer (SSL) technology protects user information using both server authentication and data encryption, ensuring that user data is safe, secure, and available only to authorised persons. SurveyMonkey® is PCI-DSS compliant [47].

### Statistical analysis

#### Sample size estimation

Different proportions of expected drop-out are reported in Table 3. Confidence intervals are computed under this expected proportions assuming 1,000 patients will be recruited.

**Table 3 Tab3:** **Different proportions of expected drop-out and confidence intervals**

**Patients recruited**	**Adherence (%)**	**Patients adherent to the treatment**	**95% Confidence interval**
1000	95	950	93.5% - 96.3%
1000	90	900	88.0% - 91.8%
1000	85	850	82.6% - 87.2%
1000	80	800	77.4% - 82.4%
1000	75	750	77.7% - 72.2%
1000	70	700	67.1% - 72.8%
1000	65	650	62.0% - 68.0%
1000	60	600	56.9% - 63.1%

#### Data analysis

The primary objective will be summarised as a proportion ± confidence interval 95% (binomial method).

The influence of potential predictors on lack of adherence or discontinuation from the therapy will be explored using a logistic regression. The effect of the hierarchical structure of the data (participants *nested in* centres *nested in* countries) on the results will be eventually explored using multilevel analyses.

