## Discussion

Adherence to AIT is an area that requires further investigation as the data currently available is mainly from clinical trials with only a limited number of real life studies and even fewer prospective studies [33,48-50].

This project will provide an insight into this important issue. It will enable an estimation of the rate of adherence to AIT in daily clinical practice for respiratory allergic disorders and Hymenoptera venom allergy. Furthermore, it will allow identification of possible reasons for lack of adherence and discontinuation of treatment. This will provide useful information for changing or modifying clinical behaviours and attitudes towards immunotherapy, in order to improve adherence wherever possible.

The main strengths of this survey are:As a multi-country survey a large number of participants will be recruited and adherence of AIT in a large part of Europe will be assessed. Given the significant number of participants included, the conclusions drawn are more likely to be applicable to a wider population. At the same time, it will enable identification of inter-country differences regarding the use of different routes of administration and reasons for discontinuation.Sharing the same methodology by all participating centres will allow for more reliable and comparable results.In addition to AIT for respiratory allergies, adherence to Hymenoptera venom immunotherapy will also be addressed in this survey. Possible contributing factors leading to lack of adherence or discontinuation will be explored in detail such as extract used, schedule, responsible insect, severity of index reaction and any side effects to AIT.

The use of online survey software has enabled us to make this survey a reality and reach clinicians in 8 different countries. Following the end of the enrolment period, over 1,350 participants have now been enrolled by 45 centres. The main allergens for which participants are having AIT include grass pollens 33.9%, house dust mite 32.3% and 15.3% Hymenoptera venoms. Preliminary one-year follow up data shows that 11.1% of participants have missed on average 2 doses in 4 months whilst less than 2% of participants have discontinued treatment.

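### The primary adherence rate is given a plain binomial 95% CI that treats participants as independent although they are nested in 45 centres and eight countries; any positive within-centre correlation makes it too narrow

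*Protocol article*

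**What the plan says.** The protocol article's Data analysis section fixes one interval for the primary objective: "The primary objective will be summarised as a proportion ± confidence interval 95% (binomial method"). The Sample size estimation section uses the same idea for planning: "Confidence intervals are computed under this expected proportions assuming 1,000 patients will be recruited". Table 3 then lists eight adherence rates, from 95% down to 60%, each with a 95% CI.

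The last sentence of Data analysis recognises the three-level structure (participant, centre, country) and says that its effect on the results "will be eventually explored using multilevel analyses". It follows the sentence on logistic regression for predictors.

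Other sections describe the clusters:
- Survey design: "The survey will take place in eight countries".
- Discussion: "over 1,350 participants have now been enrolled by 45 centres".
- Objectives: the primary rate is to be estimated "in a three year period in real life across different European countries", and a secondary aim is to "explore possible reasons for differences in adherence rates in different countries and different individuals".
- Questionnaire design: follow-up of sublingual patients differs between countries, and the extra sources used to improve reporting of missed doses depend on national practice.
- Participant selection and procedure: the local physician completes each follow-up form.

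**The concern.** A binomial interval has its nominal coverage when each participant is an independent draw. Here participants in one centre share a physician who records the outcome, a clinic routine for follow-up and national arrangements. The article itself expects adherence to differ by country. These are the usual sources of positive correlation within clusters.

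With such correlation, the variance of the overall proportion exceeds the binomial variance and the stated interval is too narrow. Estimating this rate is the primary objective, and the Discussion expects the conclusions to carry over to a wider population. The interval is what tells the reader how firmly the rate is known, so understating its width matters even in a survey without a hypothesis test.

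**Working it through.** **Step 1: reproduce Table 3.** Exact (Clopper-Pearson) 95% limits with n = 1,000 independent participants:

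| Adherent | Computed (%) | Table 3 (%) |
|---|---|---|
| 950 | 93.46 to 96.27 | 93.5, 96.3 |
| 900 | 87.97 to 91.79 | 88.0, 91.8 |
| 850 | 82.63 to 87.16 | 82.6, 87.2 |
| 800 | 77.38 to 82.44 | 77.4, 82.4 |
| 750 | 72.19 to 77.66 | 77.7, 72.2 (printed in reverse) |
| 700 | 67.05 to 72.83 | 67.1, 72.8 |
| 650 | 61.95 to 67.96 | 62.0, 68.0 |
| 600 | 56.89 to 63.05 | 56.9, 63.1 |

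All 16 limits agree. Table 3 is therefore correct under independence and contains no allowance for clustering.

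**Step 2: inputs for the clustered calculation.**
- From the article: 45 centres and about 1,350 enrolled, so m = 1,350/45 = 30 per centre.
- Chosen for illustration: adherence p = 0.80, one of the Table 3 rows.
- Assumed, because the article gives no figure: ICC from 0.01 to 0.0625. Since ICC = SD²/[p(1 − p)], these correspond to a between-centre SD of true adherence of √(0.01 × 0.16) = 4 points and √(0.0625 × 0.16) = 10 points.

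**Step 3: formulas, equal centre sizes.** Design effect DE = 1 + (m − 1) × ICC. Effective n = 1,350/DE. Half-width = 1.96 × √[p(1 − p) × DE/1,350]. Real coverage of the naive interval = 2Φ(1.96/√DE) − 1.

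| ICC | DE | Effective n | Half-width (points) | Coverage of naive 95% CI |
|---|---|---|---|---|
| 0 | 1.00 | 1,350 | 2.1 | 95% |
| 0.01 | 1 + 29 × 0.01 = 1.29 | 1,047 | 2.4 | 92% |
| 0.02 | 1.58 | 854 | 2.7 | 88% |
| 0.05 | 2.45 | 551 | 3.3 | 79% |
| 0.0625 | 1 + 29 × 0.0625 = 2.81 | 480 | 3.6 | 76% |

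**Step 4: simulation.** Beta-binomial centres, 4,000 replicates, at ICC 0.016 and 0.0625. With equal centres the Clopper-Pearson interval covered about 90% to 91% and 77%. With unequal centres (assumed size CV 0.7) it covered about 87% to 88% and 69% to 71%. A centre-cluster-robust interval on the logit scale, without country strata, covered about 94% to 95%.

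**Step 5: does over-enrolment rescue the Table 3 widths?** The width planned for 1,000 independent participants is still reached when 1,350/DE ≥ 1,000, that is DE ≤ 1.35, so ICC ≤ 0.35/29 = 0.012. Above that it is not.

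**Step 6: a small primary subgroup.** The Discussion puts Hymenoptera venom at 15.3% of enrolment: 0.153 × 1,350 ≈ 207 participants, or about 4.6 per centre if spread evenly over 45 centres (assumption). The design effect is then 1 + 3.6 × 0.01 = 1.04 to 1 + 3.6 × 0.0625 = 1.22, and naive coverage is about 95% to 92%.

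**The case against.** **The size is not in the documents.** No ICC is given. A reader might infer that the interval is certainly too narrow by a known amount; the article does not support that. Only the direction is settled, and only if the ICC is above zero. At ICC 0.01 the shortfall is modest. This stands, and the size is stated here as conditional.

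**The hierarchy is mentioned.** The multilevel sentence is separate from the predictor sentence and speaks of the results in general. A reader might say that the plan confines clustering to the predictor model; the wording does not say so, and the sentence may extend to the primary rate. Even on that reading it is tentative and exploratory, and the named primary interval remains binomial.

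**Table 3 is nearly met.** A reader might conclude that the planned precision is lost. With 1,350 enrolled it is not lost below an ICC of about 0.012, and at ICC 0.016 the half-width at 80% is 2.6 points against about 2.5 planned. Enrolment has also closed, so restating the table changes no design decision. This stands as a reason for a light touch on Table 3. It does not rescue the final interval, which will be computed on the enrolled number.

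**One pooled rate is not the whole objective.** Inhalant (both routes) and venom rates are named separately, and coverage of 76% does not apply to all of them. This stands; Step 6 shows the smaller effect for venom. Concentration of venom patients in few centres would raise it.

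**It is a descriptive survey.** No test or threshold hangs on the interval, the point estimate is unaffected, and 0.3 to 1.5 extra points per side is small beside the 7% to 97% range of earlier studies in Tables 1 and 2. This bears on severity, not on whether the method fits the data.

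**Conclusion.** The concern holds in conditional form. The plan names an interval that assumes independence for data it describes as hierarchical, and the exploratory multilevel sentence does not replace that interval. This is a stated choice of method, not a detail left to another document.

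The figures (half-width 2.4 to 3.6 points instead of 2.1, real coverage about 92% to 76%) rest on 80% adherence, 45 equal centres of 30 and an assumed ICC of 0.01 to 0.0625. Unequal centres make the shortfall worse. If the eight countries are treated as fixed strata, only centre variation within countries counts, and the article gives no value for that either. If they are treated as a sample of Europe, country-level correlation adds to the problem.

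Severity: should be fixed. The estimate itself is sound and the correction can be made at analysis.

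**What to change.** 1. In Data analysis, replace the binomial method with a centre-cluster-robust 95% CI on the logit scale for each primary rate. Without country strata, use a t reference with centres minus 1 degrees of freedom (45 − 1 = 44). If country is treated as a fixed stratum, use centres minus countries (45 − 8 = 37) and pool any single-centre country with another. State which is chosen. The simulation above tested only the unstratified version.
2. Report the observed ICC with each rate.
3. Label Table 3 as assuming independent participants, or add a design-effect column (for example 1.5, 2 and 3).

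The cost is one sentence, a table note and a few lines of code. No new data are needed, because the Data management section already builds centre and country into each participant code. The downside is a somewhat wider interval.

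### Three-year discontinuation is analysed without the timing of stopping or the partial follow-up that the survey collects; the proportion is biased if follow-up lapses

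*Protocol article*

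**What the plan says.** The primary objective (protocol article, Objectives) is "to prospectively evaluate the rate of adherence to AIT for inhalant allergies" and for Hymenoptera venom allergy over three years. The Data analysis section fixes two methods. For the first: "The primary objective will be summarised as a proportion ± confidence interval 95% (binomial method"). For predictors: "The influence of potential predictors on lack of adherence or discontinuation from the therapy will be explored using a logistic regression". Multilevel analysis of participants within centres within countries may follow. No method that uses time is named.

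The data have a time structure. Under Participant selection and procedure: "For each participant an online follow up adherence form will be completed by the local physician every 4 months", and "The last adherence follow-up form will be completed at 36 months from AIT initiation". The same section says of the discontinuation form: "This includes questions including the timing and any identified reasons for stopping AIT". The enrolment form records when AIT began (Questionnaire design). Survey design explains the three-year length by the worry that "adherence initially may be relatively good but this may decrease as time passes".

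**The concern.** A proportion of participants adherent at 36 months, and a logistic model on that status, each reduce three years to one yes or no. Two things follow.

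- **Information is given up.** Someone who stops at month 5 and someone who stops at month 33 look the same. The possible decline over time that justified the long follow-up cannot be seen.
- **Partial follow-up has no natural place.** A participant followed without stopping to month 20, whose forms then cease, has an unknown 36-month status. Any rule that places this person in the numerator, in the denominator only, or in neither moves the estimate.

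Some lapse is foreseeable. The forms are filled in by "physicians who have to complete these forms in their own time without any specific funding", and 36/4 = 9 are due per participant, or 9 × 1,350 = 12,150 over the enrolled cohort.

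**Working it through.** **Step 1: the plan's own figure.** Table 3 gives 95% intervals for adherence of 60% to 95% with 1,000 patients. Exact (Clopper-Pearson) limits reproduce all eight rows to 0.1 point. For 800 of 1,000 they are 77.38% to 82.44%, against 77.4% to 82.4% printed. Every recruited patient is in the denominator, so the stated precision assumes complete data.

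**Step 2: half-widths for comparison.**
- n = 1,000, from Table 3: (82.4 - 77.4)/2 = 2.5 points at 80%; (63.1 - 56.9)/2 = 3.1 points at 60%.
- n = 1,350 (enrolment given in the Discussion), normal approximation: 1.96 × √(0.8 × 0.2/1,350) = 2.1 points at 80%; 1.96 × √(0.6 × 0.4/1,350) = 2.6 points at 60%.

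**Step 3: effect of random loss.** The article gives no loss rate, so L (the three-year probability of loss in the absence of stopping) is an assumption, taken as 5%, 10% and 20%. True persistence S is 80% or 60%, both rows of Table 3. Hazards are constant and loss is independent of stopping:

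- h = -ln(S)/3 and l = -ln(1 - L)/3
- observed stops: D = h/(h + l) × (1 - exp(-3(h + l)))
- still treated and followed at 36 months: R = exp(-3(h + l)) = S(1 - L)
- lost counted as persisting: 1 - D; lost excluded: R/(R + D); lost counted as stopped: R

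For S = 0.8 and L = 0.2 the two hazards are equal, so D = 0.5 × (1 - 0.64) = 0.18 and R = 0.64. The three results are 82.0%, 0.64/0.82 = 78.0% and 64.0%.

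| True persistence | Loss | Lost = persisting | Lost excluded | Lost = stopped |
|---|---|---|---|---|
| 80% | 5% | 80.5% | 79.6% | 76.0% |
| 80% | 10% | 81.0% | 79.1% | 72.0% |
| 80% | 20% | 82.0% | 78.0% | 64.0% |
| 60% | 20% | 63.8% | 57.0% | 48.0% |

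Under the same assumptions Kaplan-Meier targets the true 80% or 60%.

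**Step 4: loss that reflects stopping.** Assume that 20% are lost, 80% of those retained persist, and 60% of the lost have in fact stopped. The truth is 0.8 × 0.8 + 0.2 × 0.4 = 72%. Excluding the lost gives 80% (+8 points). Counting them as persisting gives 0.64 + 0.20 = 84% (+12). Counting them all as stopped gives 64% (-8). Censoring them in a Kaplan-Meier analysis does not remove this bias.

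**The case against.** Much of the case on the other side stands.

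- **The primary outcome is adherence, not discontinuation.** It includes missed doses, which a survival method does not address. The point is therefore confined to the stopping component.
- **There is no planned censoring.** Everyone has the same 36-month window from their own AIT start. With complete follow-up both named methods are valid, and a time-to-event analysis then adds information without correcting an error.
- **Loss is not certain.** The article describes measures against it. The co-ordinators aim for complete forms for everyone enrolled (Survey progress). For SCIT, the physician is said to know of every missed dose or stop, and pharmacy records, appointments and telephone contact supplement reporting (Questionnaire design). Loss is foreseeable, no more.
- **The article does not fix how lapsed participants are counted.** A reader might infer that they must be counted as adherent or dropped, but nothing says so. They could also be counted as stopped, or imputed. That rule may sit in a fuller document, and its absence from an article is not a fault.
- **The error may be small.** At 5% to 10% random loss it lies well inside the half-width, and allowing for centre clustering would normally widen the interval further.
- **Kaplan-Meier does not cure informative loss.** Protection there comes from the bound, which could equally be put on a plain proportion.

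What the objection does not remove is the choice of method. The two analyses named for this outcome leave unused the timing that the survey goes to the trouble of collecting.

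**Conclusion.** The point holds as a choice of method worth improving, with a bias that is conditional on loss. If follow-up is complete, the stated analyses are valid but say nothing about when participants stop. If follow-up lapses at random, with 80% true persistence, the proportion is off by about 0.5, 1 or 2 points at 5%, 10% or 20% loss: upward if the lost count as persisting, downward if they are excluded. The half-width there is 2.1 to 2.5 points. At 60% persistence and 20% loss the error is +3.8 or -3.0 points, against a half-width of 2.6 to 3.1. Counting the lost as stopped, or loss that itself reflects stopping, gives larger errors: 16 points (80% against 64%) in the first case at 80% persistence and 20% loss, and 8 to 12 points in the Step 4 example. All of this rests on assumed loss rates and, for random loss, on constant and independent hazards.

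A reader might also infer that the preliminary one-year discontinuation of under 2% (Discussion), set against one-year adherence of 47% and 65% in two Table 1 studies, points to unreported stops. The documents do not support that. Discontinuation and adherence are different measures, the 47% study was in children and the 65% study mixed children with adults, whereas this survey enrols adults. Tables 1 and 2 also contain three-year adult figures of 88% and 85%.

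**What to change.** - **Dose adherence (primary objective).** Keep the proportion with its binomial interval, and report it also by 4-month interval.
- **Discontinuation.** Estimate persistence by Kaplan-Meier from AIT start, reported at 12, 24 and 36 months, censoring at the last received form when follow-up lapses.
- **Predictors of discontinuation.** Replace the logistic regression by a discrete-time (4-monthly) or Cox hazard model with centre and country effects. The discrete-time form suits the data, because the forms come every four months and the article promises the timing of stopping, not an exact date.
- **Bound.** Because censoring may be informative, repeat the persistence estimate with every lapsed participant counted as discontinued at the first missing form.

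The cost is analysis wording and a little more analysis work; the forms already collect the data. The downside is an assumption of non-informative censoring, which the bound tests.
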